### Data management

3.2

The researchers stored all trial-related information, including subject identification codes, source data, and investigator files, along with associated communications, in a dedicated database for the study. Upon completion of the trial, the source data within the database and all pertinent study documents will be preserved in compliance with legal and regulatory requirements.

### Safety

3.3

All adverse events (SAEs) or adverse events (AEs) reported by patients or detected by investigators will be collected during the trial period and must be recorded on the corresponding pages of the registry. All SAEs and AEs that occur after the patient signs the informed consent form will be recorded on the pages of the registry. All patients with SAEs and AEs must be monitored to determine the outcome. The trial must be reported to the principal investigator within 24 hours after the occurrence of SAEs and AEs. The initial report must be as complete as possible, including detailed information on the current SAEs and AEs in the trial (severe), as well as the assessment of the causal relationship between the events and the trial, and the occurrence of the events. The principal investigator will notify the trial monitor of serious SAEs upon request and is responsible for promptly reporting any serious SAEs or AEs to the ethics committee.

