### Trial design and setting

2.1

The research will be conducted at the Inner Mongolia Maternity and Child Health Care Hospital in China from March 2025 to September 2025, employing clinical reagent testing and internationally recognized scales for quantitative investigation.

The study population consists of families of children with PKU, who will be divided into two groups: Group A will be the mHealth intervention group, while group B was the control group. The intervention group will receive mobile health interventions through WeChat group chats. The control group, on the other hand, will simply get regular health education, which includes an oral presentation on PKU by a professional physician at the time of enrollment, educating the parents of PKU children on how to manage their diets low in phenylalanine. A printed handbook on PKU disease and daily management knowledge will also be given to them, but they won’t have access to online education and training, frequent reminders for monitoring, or online consultation services.

The intervention will last for 6 months, with clinical indicators, intelligence tests, and questionnaire surveys being conducted at baseline, as well as at 3 and 6 months after the start of the intervention to examine the effectiveness of the intervention on the health management of children with PKU. The flow chart of the study is shown in **Figure 3** and **Table 1**.

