#### Stage 3: determine intervention content and implementation options—mobile health intervention based on the WeChat

2.6.3

Based on the analysis and selections from the previous two stages, and after comprehensively considering affordability, practicability, effectiveness acceptability, safety, and equity, the final decision is to utilize WeChat group chats for remote mobile health intervention. The group chat will incorporate the following four functions to achieve the seven interventions outlined in Stage 2:

*Health education module and real-time reminder function*. Through the WeChat group, educational materials in various formats (e.g., illustrations, videos) will be distributed weekly to provide PKU knowledge and health education. Topics include basic disease knowledge, the importance of health management, low-Phe diets, and regular follow-up monitoring. Personalized reminder notifications will also be set up to encourage timely completion of dietary records and regular medical check-ups.
*Diet uploading and phenylalanine content query function*. Parents will input the types and quantities of food consumed by their child each day into the WeChat group chat. The system will automatically calculate the daily Phe intake, notify parents if the intake exceeds the recommended limit, and provide adjustment suggestions. Additionally, the WeChat group will include a built-in food Phe database containing Phe content for common foods across three meals, along with recommended low-Phe meal combinations.
*Regular feedback and incentive mechanism*. The group chat will record the dietary logs and compliance status uploaded by parents. At the end of each month, virtual rewards such as badges and titles will be issued based on the monthly records to motivate parents to continue maintaining healthy management behaviors.
*Family interaction and online consultation function*. Parents can interact with other PKU families in the group chat to share health management experiences. Additionally, the group chat will offer an online consultation feature, allowing parents to seek advice from professional physicians in the group at any time.

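### Adverse event capture depends on report or detection, and only the WeChat arm has a physician channel between visits, so event counts shown by arm are at risk of detection bias

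*Protocol article*

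**What the plan says.** Section 3.3 (Safety) states how AEs enter the record: those "reported by patients or detected by investigators will be collected during the trial period". The scope is the same for both arms: "All SAEs and AEs that occur after the patient signs the informed consent form will be recorded on the pages of the registry". The section also asks for a report to the principal investigator within 24 hours of occurrence and for follow-up of affected patients to outcome.

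Contact between visits differs by design. In the WeChat arm (section 2.6.3), "Parents will input the types and quantities of food consumed by their child each day into the WeChat group chat", and the group offers online consultation, "allowing parents to seek advice from professional physicians in the group at any time". Controls receive an oral presentation and a handbook at enrolment, but "they won’t have access to online education and training, frequent reminders for monitoring, or online consultation services" (section 2.1).

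Both arms share the assessments, described as "being conducted at baseline, as well as at 3 and 6 months after the start of the intervention" (section 2.1). Section 3.1 has hospital physicians gather all data. Tables 1 and 2 itemise the assessments at each time point; AE enquiry is not among them.

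**The concern.** An event is recorded only if a family mentions it or an investigator notices it, so the chance of recording depends on how easily a family can reach a trial physician. The intervention supplies such a route to one arm. A feverish illness or feeding problem in month 2 can be raised in the WeChat group the same day. In the control arm it may surface only at the month 3 visit, if the family thinks to mention it, since no question is described that would prompt them.

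Two things are at stake. First, a table of AEs by arm would mix true frequency with ease of reporting. The intervention could look less safe than it is, or a real excess could be explained away as better reporting. Second, whether or not AEs are ever compared, the 24-hour and follow-to-outcome rules are harder to meet for control-arm events between visits. Blinding does not help: families open their own envelopes and learn their group (section 2.4), and the Discussion accepts that those delivering the intervention cannot be blinded.

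**Working it through.** **Step 1. Opportunity for capture, by arm**

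| Route | WeChat arm | Control arm | Section |
|---|---|---|---|
| 3- and 6-month assessments by physicians | yes | yes | 2.1, 2.8, 3.1 |
| Scheduled blood tests and growth measures | yes | yes | 2.8, Table 2 |
| Daily food log, answered by the system | yes | no | 2.6.3 |
| On-demand consultation with physicians | yes | no | 2.1, 2.6.3 |
| Fixed AE questions at visits | not described | not described | 3.3, Tables 1 and 2 |

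Laboratory and growth problems have the same scheduled detection in both arms. The imbalance concerns events that must be told to someone between visits.

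**Step 2. Inputs for size.** From section 2.3: 25 children per group, two-sided α = 0.05. The article gives no AE rate, capture fraction or safety figure to reproduce, so every rate and capture fraction below is an assumption. True AE frequency is set equal in the two arms throughout, so any significant difference is a false positive.

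**Step 3. Event counts.** Expected recorded count per arm = 25 × true AEs per child × fraction captured. Counts are taken as Poisson and compared by the exact conditional binomial test; the false-positive rate comes from exact enumeration.

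| True AEs per child | Capture, WeChat / control | Expected counts | Ratio | P < 0.05 |
|---|---|---|---|---|
| 2 | 70% / 70% | 35 / 35 | 1.00 | 4% |
| 2 | 80% / 70% | 40 / 35 | 1.14 | 7% |
| 2 | 70% / 50% | 35 / 25 | 1.40 | 21% |
| 2 | 90% / 60% | 45 / 30 | 1.50 | 37% |
| 2 | 80% / 40% | 40 / 20 | 2.00 | 70% |
| 1 | 80% / 40% | 20 / 10 | 2.00 | 37% |
| 0.5 | 80% / 40% | 10 / 5 | 2.00 | 18% |
| 0.2 | 80% / 40% | 4 / 2 | 2.00 | 5% |

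For the fifth row: 25 × 2 × 0.8 = 40 and 25 × 2 × 0.4 = 20. A single trial observing exactly 40 against 20 has two-sided P = 0.013.

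**Step 4. Children with at least one event.** Observed risk = true risk × detection probability. With detection 0.9 in the WeChat arm, true risk 10%, 30% or 50%, and a two-sided Fisher test at 25 per arm:

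| Control detection | Spurious risk ratio | Spurious risk difference | P < 0.05 |
|---|---|---|---|
| 0.9 | 0.9/0.9 = 1.00 | 0 | 0.7% to 3.2% |
| 0.7 | 0.9/0.7 = 1.29 | 2 to 10 points | 0.6% to 7.4% |
| 0.5 | 0.9/0.5 = 1.80 | 4 to 20 points | 0.8% to 22.9% |

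**Step 5. Reading.** The expected direction is the same wherever capture is unequal: more events recorded in the WeChat arm. The spurious ratio depends only on the capture gap. The chance of a significant result also depends on how common AEs are, and is low when they are rare.

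**The case against.** Three stronger readings are tempting, and the article supports none of them.

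- **Daily contact with trial physicians.** A reader might infer this from the food log. What is daily is an upload to which the software responds: "The system will automatically calculate the daily Phe intake, notify parents if the intake exceeds the recommended limit, and provide adjustment suggestions". Physicians are there on request, and nothing says they review posts daily or collect AEs from the chat.
- **A biased safety comparison.** No such comparison is planned. Safety is not listed among the outcomes in section 2.8, and section 3 names no test of AEs. Section 3.3 deals with recording, follow-up and reporting.
- **Controls cut off from reporting.** The recording rule covers both arms. Section 2.1 withholds online services, not the option of telling the hospital. Both arms attend the same visits, and controls may have other contacts, since the number of blood tests is itself counted as compliance.

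It can also be said that an article may leave an AE question form to the full protocol or case report form, and that the wording of section 3.3 is compatible with asking at visits. That is fair, and the absence of a form is not the point here. The point is that the capture rule as stated, combined with the contact pattern as stated, gives unequal opportunity. The shared visits narrow that gap but do not close it for events between them.

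Finally, the largest rejection rate needs both frequent AEs and a wide capture gap. That objection stands: the 70% is the upper end of an assumed range, not an estimate.

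**Conclusion.** The point holds in a limited form. As described, ascertainment of AEs is not equal by arm, so AE counts displayed by arm would be at risk of detection bias, probably towards more events in the WeChat arm. Control-arm events between visits may be recorded late or missed despite the 24-hour and follow-to-outcome rules.

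The size cannot be fixed from the article. Over the assumed AE rates and unequal capture fractions, spurious ratios run from 1.14 to 2.00, and the false-positive rate of a hypothetical between-arm test runs from below 5% to about 70%. The primary analysis of serum Phe and Tyr and the sample size are untouched. This is an inexpensive improvement to safety recording, not a flaw in the efficacy plan.

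**What to change.** In section 3.3, with a matching row in Tables 1 and 2:

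1. Have the physicians ask the same fixed AE questions of every family, in both arms, at the existing 3- and 6-month visits, covering the period since the last assessment.
2. Add a field to the registry page for the source of each AE: visit question, WeChat, or other.
3. If AEs are shown by arm, base the comparison on events elicited at visits. An event already reported through WeChat counts when the family also names it at the visit. List all other events separately.
4. Continue to record and act on every AE whatever its source.

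The cost is a few minutes per visit, a short question list and one registry field, with no extra visit or staff. The downside is some recall error, which should be similar in both arms because the questions and the recall period are the same. Control-arm events that nobody asked about cannot be reliably recovered after the trial.

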## Discussion

4

This study aims to develop a mobile health intervention program targeting parents’ caregivers, such as parents, to improve the health management outcomes of patients with PKU. If the effectiveness of this program is validated, several key factors may contribute to its success. First, the program is based on the internationally recognized health intervention theories. In this research, the BCW theory and the family health theory framework are integrated. According to the six domains of family health, the BCW theory is extended to the family level. Following the structured steps of the BCW theory, the main obstacles affecting the family health behavior of PKU patients are analyzed, and appropriate intervention options are selected. Second, the program has formulated detailed, convenient, and diverse specific intervention measures. Guided by the nine intervention functions and seven policy categories of the BCW theory, the study designs a range of intervention strategies. And combined with the WeChat platform, various educational materials such as paper, pictures, and videos are designed to improve the accessibility and convenience of the intervention. Finally, the program carefully considers multiple factors that influence the outcomes. Based on existing research, this study not only examines the impact of the intervention program on metabolic, functional, and intellectual development indicators in PKU patients but also considers its effects on family members’ mental health, parenting stress, and other family-related factors. This comprehensive approach aims to design effective and minimally burdensome intervention measures, thereby facilitating the broader implementation of the program.

If this research plan proves effective, it can be extended to the health management of PKU patients in other regions of China. According to the data from the Chinese newborn screening information system from 2013 to 2017 (52), Gansu, Qinghai, Ningxia and Shanxi are among the provinces with the highest PKU incidence rates. Building on the development of PKU patient families in Inner Mongolia, a northern province, this study provides a set of referable intervention strategies for the health management of PKU patients in these provinces. Existing studies have established network-based programs for the health management of PKU patient families (35). These mobile health intervention platforms can be integrated with the theoretical model developed in this study to provide more personalized, convenient, efficient and cost-effective intervention plans for PKU patient families.

This study also has several limitations. First, due to the nature of the intervention, blinding of the interventionists is not feasible. To mitigate this limitation, detailed training and standardized intervention manuals will be provided to minimize subjective bias among intervention personnel, thereby ensuring consistency in the implementation of intervention measures. Second, some outcome measures rely on self-reported date from participants, which may introduce bias and affect the reliability of the results.
